## Abstract

**Introduction:**

Migraine is a disabling, recurrent headache disorder with complex comorbidities. Conventional treatments for migraine are unsatisfactory, with side effects and limited effectiveness. Chinese herbal medicine (CHM) has been used as an alternative or complementary treatment option for migraine in China. Currently, the existing evidence of benefit of CHM for migraine has been generated from randomised clinical trials using standardised intervention with a focus on internal validity hence with limited external validity. Moreover, CHM individualised intervention design, patients’ preferences and concerns, and clinicians’ experience are critical to clinical decision making and therapeutic success. This real-world observational study aims to gather practice-based evidence of effects and safety of CHM for migraine in the context of integrating Chinese medicine diagnostic procedures, patients’ preferences and matters relevant to clinical decision making.

**Methods and analysis:**

The study is being undertaken at the Guangdong Provincial Hospital of Chinese Medicine (GPHCM) from December 2020 to May 2022. We anticipate that approximately 400 adult migraineurs will be enrolled and observed on their migraine severity, analgesic consumption, quality of life, anxiety, depression and insomnia at baseline and then every four weeks over 12 weeks. Treatments, diagnostic information, and patient-reported most bothersome symptoms will be collected from patient clinical records. Patient’s demographic data, preferences and concerns on CHM treatments will also be gathered at baseline and be analysed. Factors related to clinical outcomes will be explored with multiple correlation and multivariable regression analyses. Effects of CHM will be evaluated using generalised estimated equation, based on clinical outcome data.

**Discussion:**

This study will provide comprehensive evidence of CHM for migraine in the context of evidence-based practice.

**Trial registration number:**

ChiCTR2000041003

## Introduction

Migraine is a recurrent, severe and primary headache disorder, manifesting unilaterally, throbbing in nature, and lasting 4 to 72 hours [1]. Migraine presented with a global age-standardised prevalence of 14.4% and was ranked as the second most disabling disease in 2016, with an estimated years of life lived with disability (YLDs) of 45.1 million [2]. In China, the number of migraineurs was estimated to be 132 million, with six million YLDs, in 2017 [2, 3].

According to the International Classification of Headache Disorders, 3^rd^ edition (ICHD-3) [1], migraine is typically divided into migraine with aura and migraine without aura. Migraine can also be categorised as episodic or chronic, according to its frequency. However, episodic migraine can progress to chronic migraine at an annual rate of 2.5% [4].

Migraine patients are more likely to suffer from psychiatric disorders including depression and general anxiety disorder [5, 6], as well as sleeping disorders such as insomnia [7]. These comorbidities are more commonly seen in chronic migraine compared with episodic migraine [8], and also in migraine with aura compared with migraine without aura [9, 10]. Furthermore, the comorbidities in episodic migraine indicate a poor prognosis, leading to poorer quality of life and limiting the response to treatments [7, 11], and also increase the risk of progression to chronic migraine and medication-overuse headache [1, 12, 13].

Migraine is usually managed with medications for relieving symptoms in the acute stage, and with prophylactic treatment for reducing the frequency and severity of future attacks. The acute medications include aspirin, nonsteroidal anti-inflammatory drugs, paracetamol, antiemetics, steroids, and triptans. Prophylactic pharmacotherapies include calcium channel blockers, beta-blockers, tricyclic antidepressants, candesartan, pizotifen, angiotensin-converting enzyme inhibitors, selective serotonin reuptake inhibitors (SSRI), serotonin norepinephrine reuptake inhibitors (SNRI), antiepileptics, Botulinum toxin A and calcitonin gene-related peptide (CGRP) [14, 15]. Among them, only tricyclic antidepressants, SSNI and SNRI can be adopted for migraine comorbid with depression [14–16]; Botulinum toxin A is suggested for chronic migraine. Medical devices for migraine include occipital nerve block, vagus nerve stimulation, transcutaneous supraorbital nerve stimulation and transcranial magnetic stimulation [14–16]. However, approximately 30–40% of migraineurs are dissatisfied with current treatments, especially those suffering from chronic migraine [17, 18] and migraine with comorbidities [19–23], citing insufficient treatment effects, low tolerability, and unbearable side effects [24].

Acknowledging the above-mentioned limitations, there is an urgent need to identify alternative or complementary therapies to assist current conventional managements. Chinese herbal medicine (CHM), which is often prescribed to migraine patients in China [25], has gained clinical research evidence as an effective alternative or complementary therapy for migraine in recent years. However, most of the existing evidence has been generated from randomised controlled trials (RCTs) [26–30] and RCT-based systematic reviews [31–34]. Under controlled settings, RCTs usually apply strict selection criteria and provide unified treatments to all participants [35]. Such design may not reflect the complexity of migraine and its comorbidities [36], nor reflect the real-world practice of CHM which is commonly tailored according to individual’s syndrome differentiation [37]. Hence, the research evidence obtained from previous explanatory RCTs and systematic reviews need to be supplemented with more real-world evidence.

To address this research gap, observational studies, which reflect real-world settings and evaluate both standardised outcomes and patient-reported most bothersome symptoms (MBS), can be a pragmatic approach to assess the effects and safety profiles of CHM for migraine and its comorbidities, and provide valuable information for decision making in CHM clinical practice. In line with this, we designed this prospective, registry-based, real-world observational cohort study.

## Objectives

This observational study aims to 1) evaluate the effects and safety of individualised CHM for adult migraine in a real-world setting; 2) identify factors that contribute to clinical outcomes of CHM for migraine; 3) summarise the common patterns of CHM for migraine and its comorbidities; and 4) report on the characteristics of migraine patients who seek CHM management, including their preferences and concerns associated with CHM therapies for their migraine.

## Methods

### Study design

This prospective, registry-based, observational cohort study is being undertaken at the Headache Clinics at the Guangdong Provincial Hospital of Chinese Medicine (GPHCM) in southern China [38]. Participant recruitment commenced in December 2020 and is targeted to end in May 2022. Based on consecutive sampling, an estimated number of 400 eligible migraineurs will be recruited.

All participants will be required to complete case report forms (CRFs) every four weeks over a period of 12 weeks. Following the same period intervals, data regarding participants’ detailed treatment plan, including medications, administrative methods, courses, dosage and forms of CHM, which have been determined by their headache specialists, will also be collected from their clinical records. Data will be collected for the entire study duration, even in cases where treatments have been discontinued before the end of the observation period.

The study (version 1.0) was approved by the ethics committee of GPHCM (ZE2020-243-01) and registered with the Human Research Ethics Committee of RMIT University (24235). This study complies with the Declaration of Helsinki, Ethical Guidelines for Medical Research on Humans, and Good Clinical Practice guidelines. The protocol has been registered in the Chinese Clinical Trial Registry (No. ChiCTR2000041003). The reporting of this study will abide by the Strengthening the Reporting of Observational Studies in Epidemiology (STROBE) statement for cohort studies [39].

#### Eligibility criteria

Participants will be eligible for registration if they meet the following criteria:

a). diagnosed with migraine according to the ICHD-3 (1); b). first time seeking treatment for migraine in GPHCM; c). able to provide written informed consent; d). aged of 18 years old or above; and e). not concurrently participating in other interventional trials.

Participants will be excluded for registration and participation if they have any of the following conditions: a). diagnosed with diseases which could induce migraine-like headache such as glaucoma, brain tumour, brain injury; b). diagnosis of migraine being corrected to secondary headaches during the observation period; c). severe impairment of speech, vision, memory or cognition that affects communication and ability to complete questionnaires; d). pregnant or breastfeeding; or e). highly dependent on medical care.

Participants will be marked as drop-outs if they request to withdraw from the observation for any reason.

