#### Exposures and confounders

In this real-world observational study, CHM treatment is defined as the main exposure. Participants being treated with CHM solely and those treated with a combination of conventional prophylactic treatment and CHM will be considered as two subcohorts for analyses.

Measured confounders in this study include comorbidities of migraine (depression, anxiety and insomnia, evaluated by PHQ-9, GAD-7, and ISI, respectively), gender, baseline severity of migraine (duration, average frequency, average pain NRS and analgesics consumption at entrance), association with the menstrual cycle (pure menstrual migraine vs menstrually related migraine vs non-menstrual migraine), and aura (migraine with aura vs migraine without aura).

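### Entry defines patients new to the hospital, not new to CHM, and nothing planned separates those already taking CHM, so baseline may already be affected by the exposure for some participants

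*Protocol article*

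**What the plan says.** All references are to the protocol article.

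- **Eligibility criteria.** Inclusion criterion b) is "first time seeking treatment for migraine in GPHCM". Exclusions a) to e), the last being patients "highly dependent on medical care", do not mention current or recent CHM. No washout is set.
- **Introduction.** CHM is described as a common prescription for migraine in China.
- **Exposures and confounders.** "In this real-world observational study, CHM treatment is defined as the main exposure". The only split by treatment is this: "Participants being treated with CHM solely and those treated with a combination of conventional prophylactic treatment and CHM will be considered as two subcohorts". The listed confounders are depression, anxiety and insomnia, gender, baseline severity, menstrual association and aura. Baseline severity includes "average frequency, average pain NRS and analgesics consumption at entrance". Prior CHM is not on the list.
- **Data collection.** Response is a halving of attack frequency. Adverse events are what participants report at the observational visits. Medical history is taken at enrolment on a structured form (S1 File), which is not among the documents reviewed.
- **Analytical methods.** The effect of CHM is judged by generalised estimating equations on longitudinal outcomes, with a disease risk score for measured confounders and instrumental variables for unmeasured ones.
- **Discussion.** The absence of a run-in is admitted as a limitation and linked to recall bias and confounding. Prior CHM is not mentioned.

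**The concern.** Being new to a hospital is not the same as being new to a treatment that is widely available elsewhere. For a patient who arrives on CHM, the change from T0 measures continuing or switching CHM, not starting it. Four quantities serving the first objective (effects and safety) are exposed to this:

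1. **Mean change from baseline.** It is measured from a level that prior CHM may already have moved.
2. **The 50% response rate.** A lower treated baseline makes halving harder to reach.
3. **Adjustment for severity at entry.** In a continuing user that severity may be a result of the exposure, so adjusting for it can remove part of the effect.
4. **Adverse-event incidence.** Reactions to CHM begun before enrolment fall outside the visits, and people who tolerated it badly may already have stopped.

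The comparison of the two subcohorts is also affected if the share of prior users differs between them.

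**Working it through.** The article gives no figure that depends on this point. The planned 400 is a clinic-volume estimate without alpha, power or effect size, so there is nothing to reproduce. What follows illustrates scale under stated assumptions.

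**Inputs.** From the article: about 400 participants; response threshold 50%. Assumed, because the article is silent:
- p, the share on CHM at T0: 10% to 50%.
- f, the fraction of the CHM effect already present at T0 in those patients: 0.5, with 1 as the extreme.
- Adverse-event risk in new users: 10%.
- k, the risk in continuing users relative to new users: 0.5.

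**Mean change.** Let D be the change in new users. A continuing user has f·D behind them at T0 and shows (1 − f)·D. The pooled mean change is (1 − p)·D + p·(1 − f)·D = D·(1 − p·f).

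| p | Patients of 400 | f = 0.5 | f = 1 (extreme) |
|---|---|---|---|
| 10% | 40 | 0.95 | 0.90 |
| 20% | 80 | 0.90 | 0.80 |
| 30% | 120 | 0.85 | 0.70 |
| 50% | 200 | 0.75 | 0.50 |

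With p = 0 there is no bias.

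**Response.** Let e be the full relative reduction from the untreated frequency. Measured from a baseline that already holds a fraction f of it, the observed reduction is e·(1 − f)/(1 − f·e). A patient exactly at the threshold (e = 0.5) with f = 0.5 shows 0.25/0.75 = 33% and counts as a non-responder. To reach an observed 50% with f = 0.5, e must satisfy 0.5·e = 0.5·(1 − 0.5·e), so e = 67%.

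**Subcohort comparison.** If both subcohorts have the same true change D but prior-user shares p1 and p2, the apparent difference is D·f·(p2 − p1). With 10% against 30% and f = 0.5, that is 0.5 × 0.20 = 0.10 of D.

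**Adverse events.** Observed risk = 10% × [(1 − p) + p·k]. With k = 0.5 this gives 9.5%, 9.0%, 8.5% and 7.5% for p = 10%, 20%, 30% and 50%.

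**Direction.** The formulas cover only the case in which prior CHM had helped. A patient who comes because earlier CHM failed has f near 0 but may be a poorer responder. A patient who switches to a formula that suits better may show a full change or more. The pooled result could move either way.

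**Do the planned adjustments help?** A disease risk score built from the listed confounders does not contain prior CHM and does contain severity at entry. Instrumental variables address unmeasured confounding of treatment choice. Neither turns a treated baseline into an untreated one.

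**The case against.** The strongest defence is that the entry criterion sets a coherent time zero of its own: the start of individualised care at this clinic. The first objective concerns CHM in routine practice, and patients with earlier treatment belong to that population. This stands. It is a reason not to narrow eligibility and to keep the pooled result as the effect of care at this clinic. It does not support reading the pooled change as the effect of CHM, which is the exposure the article names.

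A second defence is that the case report form may already ask about past treatment, and that analysis sets are commonly left to an analysis plan. The first half stands: the form is not shown, so the article cannot be faulted for failing to collect the data. The second half stands only in part. The exposure, the subcohorts and the confounders are stated in the article, and as stated they pool the two kinds of patient.

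A third defence is that the article admits the missing run-in, urges caution and tests no preset hypothesis. That lowers the stakes, but the admission does not reach prior CHM.

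Two stronger readings are tempting and not supported. A reader might infer that the plan takes T0 as the start of CHM for everyone; no section says so. A reader might also take 1 − p as the expected shrinkage. It requires patients who are seeking treatment, and who will receive a newly tailored prescription, to show no further change, so it is an extreme case.

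**Conclusion.** The point holds in a limited form. As written, the entry criterion, exposure definition, subcohorts and confounder list would mix patients starting CHM with patients already on it. This may bias the change from baseline, the response rate, the severity adjustment and adverse-event incidence. That bias is present cannot be asserted: the article gives no share of prior users, and the direction is open. With half the effect already in the baseline, the mean change would be 0.95 to 0.75 of the new-user value for shares of 10% to 50%; these figures rest wholly on the assumed p and f. The eligibility criterion itself is not an error, and the descriptive aims (treatment patterns, patient characteristics and preferences) are unaffected.

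**What to change.** - **Eligibility:** leave unchanged.
- **Baseline data:** if the case report form does not already do so, record any CHM and any conventional prophylactic taken in the four weeks before T0, and ever. For participants already enrolled, the clinical record of the first visit may supply this.
- **Exposures and confounders:** add prior CHM to the listed confounders.
- **Analysis of the first objective:** report the effect and adverse-event incidence separately for new users and for continuing or switching users. Rest any statement about starting CHM on the new-user stratum, and describe the pooled result as the effect of care at this clinic.

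**Cost.** One or two baseline questions and one defined stratification; enrolment and care do not change. The price is precision. With equal variance and no losses, interval width in the new-user stratum grows by √(400/n): for p = 10% (n = 360) by a factor of 1.05, for p = 30% (n = 280) by 1.20, and for p = 50% (n = 200) by 1.41.

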#### Interventions

Participants will receive individually tailored treatment determined by their headache specialist in the GPHCM; these include CHM in the form of herbal decoction, granules or patented pill, alone or in combination with western medicine or other treatment procedures such as acupuncture. The treatment plan will be based on discussion between individual participants and their headache specialist, with no limitations or interference set by this study.

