#### Estimated number of patients

This study aims to explore the information related to migraine management based on a registry of the patient cohort from GPHCM available in a specific time range, sample size calculation is not required since there are no pre-determined hypotheses to be tested [49]. This study adopts the consecutive sampling method for recruitment, which is recommended to reduce selection bias in non-randomised studies [49]. The estimated number of participants is approximately 400, based on the average annually outpatient visit numbers at the headache clinic of GPHCM between July 2018 and July 2020.

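### Exclusion criterion (b) removes participants on a re-diagnosis that can only arise after enrolment, which may bias the effect estimates and would lose safety data

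*Protocol article*

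**What the plan says.** The exclusion list in the protocol article (Eligibility criteria) opens with "Participants will be excluded for registration and participation if they have any of the following conditions". Item (a) covers people "diagnosed with diseases which could induce migraine-like headache such as glaucoma, brain tumour, brain injury". Item (b) is "diagnosis of migraine being corrected to secondary headaches during the observation period". The same section counts as drop-outs only those who ask to withdraw.

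Under Study design, the article commits to follow-up after treatment stops: "Data will be collected for the entire study duration, even in cases where treatments have been discontinued". It has no matching statement for people whose diagnosis changes. Under Data collection, examination results and western diagnoses are taken from the clinical records.

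The first objective is to "evaluate the effects and safety of individualised CHM for adult migraine in a real-world setting". Analytical methods names generalised estimating equations for the effects, a disease risk score and instrumental variables for confounding, and multiple imputation for missing quantitative outcomes.

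**The concern.** Eligibility should rest on what is known at entry. Item (a) already deals with secondary causes diagnosed by then, so item (b) does its work only afterwards. Followed as written, it takes out people who were enrolled as having migraine and who will generally have begun CHM.

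This matters if the chance of being re-diagnosed depends on how the patient is doing. The article describes no common diagnostic work-up during follow-up and no independent adjudication of a changed diagnosis. It is plausible that a patient who does poorly is investigated again, while a misdiagnosed patient who improves is not. In that case the rule would remove mainly poor responders, and it would not leave a clean migraine cohort either.

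The other provisions in the article do not deal with this. Both subcohorts receive CHM, so changes over time have no CHM-free comparator in which the selection might cancel. The drop-out definition does not count these removals. The disease risk score and instrumental variables address confounding, not selection after enrolment. Imputation fills gaps for those still counted as participants and does not by itself bring back someone ruled ineligible.

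Safety is a separate issue. A person who took CHM and was later re-diagnosed still carries information about adverse events, whatever the final diagnosis.

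**Working it through.** The article has no figure to reproduce. On size it says "The estimated number of participants is approximately 400, based on the average annually outpatient visit numbers" and "sample size calculation is not required since there are no pre-determined hypotheses to be tested". It gives no re-diagnosis rate and no expected response rate. What follows is therefore a sensitivity calculation on stated assumptions.

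**Inputs**
- N = 400 (Estimated number of patients).
- Response means a 50% reduction in migraine frequency (Data collection).
- R, the response rate in all enrolled: assumed 50%, varied from 40% to 60%.
- q, the share re-diagnosed and removed: assumed 1%, 2%, 5% or 10% (4, 8, 20 or 40 of 400).
- r, the response rate among those removed: assumed 0, R/2, R or 1.25R.

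**Formula.** Response among those kept = (R − q·r)/(1 − q). The shift is this minus R.

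**Examples at R = 50%, q = 5%**
- r = 0: 0.500/0.95 = 52.6%, shift +2.6 points.
- r = 25%: (0.500 − 0.0125)/0.95 = 0.4875/0.95 = 51.3%, shift +1.3.
- r = 50%: (0.500 − 0.025)/0.95 = 50.0%, shift 0.
- r = 62.5%: (0.500 − 0.03125)/0.95 = 49.3%, shift −0.7.

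**Shift in percentage points at R = 50%**

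| Re-diagnosed (q) | r = 0 | r = R/2 | r = R | r = 1.25R |
|---|---|---|---|---|
| 1% | +0.5 | +0.3 | 0 | −0.1 |
| 2% | +1.0 | +0.5 | 0 | −0.3 |
| 5% | +2.6 | +1.3 | 0 | −0.7 |
| 10% | +5.6 | +2.8 | 0 | −1.4 |

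With R from 40% to 60% and q from 1% to 5%, the extreme case r = 0 gives +0.4 to +3.2 points. At q = 10% it gives +4.4 to +6.7.

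**Yardstick.** The standard error at R = 50% is √(0.5 × 0.5/400) = 0.025, or 2.5 points. Unlike this error, a selection shift does not shrink as N grows.

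**Between the two subcohorts** (R = 50% in both, r = 0). With equal q the difference is 0. With 5% removed in one and 2% in the other it is 0.5/0.95 − 0.5/0.98 = 0.526 − 0.510 = +1.6 points. With the rates swapped it is −1.6. The rule need not favour either subcohort.

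**The case against.** A reader might infer that item (b) preferentially removes poor responders and so flatters CHM. The article does not support that as a statement of fact. Nothing in it links re-diagnosis to response, and a re-diagnosis could equally follow a test ordered at entry whose result came back later. A calculation that assumes the re-diagnosed do worse than the rest builds in its own sign. The table above includes the cases where the shift is zero or negative.

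The phrase "with no limitations or interference set by this study" should not be read as evidence of discretionary work-up. It describes the treatment plan, not the diagnostic process. Diagnosis at entry is not loose either: it follows ICHD-3, and headache specialists trained for the study pre-screen patients.

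The rule also has a legitimate purpose. The objective concerns migraine, a corrected diagnosis may mean that the person never had it, and migraine-specific outcomes are hard to interpret in secondary headache. Whether such people belong in the main effect analysis is a choice of target population, and either answer can be defended.

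Finally, the text excludes from participation and does not say that data already collected are deleted. Analysis sets may be defined in a full protocol or analysis plan that is not shown, so their absence here is no fault. The Study design sentence on discontinued treatment does not contradict item (b), because it concerns a different event.

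All of this stands. What remains is that a post-enrolment event is written into the exclusion criteria as a condition of participation. That wording bears on what is collected, and a later analysis plan cannot recover follow-up that was never obtained.

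**Conclusion.** The point holds in a limited form. Item (b) conditions participation on information that arises after enrolment, and generally after CHM has begun. It may bias the response rate and before-after changes upward if re-diagnosis tends to follow a poor course. Whether it does, and by how much, cannot be determined from the article.

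At an assumed 50% response and 1-5% re-diagnosed, the shift is about half a standard error or less if the re-diagnosed respond half as often (at most +1.3 against 2.5 points). It is about one standard error in the extreme case that 5% are re-diagnosed and none respond. Rates near 10% would make it larger, but the article gives no reason to expect them. The loss of safety follow-up on exposed people does not depend on these assumptions about response. It does depend on the exclusion from participation being applied as written. This is a cheap improvement to the design, not a flaw that undermines the study.

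**What to change.** 1. Move item (b) out of the exclusion criteria, so that eligibility rests on information available at enrolment, and record re-diagnosis as a post-enrolment event with its date.
2. Continue data collection on these participants to the end of the 12 weeks, as the article already does when treatment is discontinued.
3. Keep their exposure and adverse events in the safety data.
4. Report their number and the timing of re-diagnosis by subcohort.
5. Present the effect analysis both for all enrolled, treated participants and without the re-diagnosed, and state in advance which is the main one. Either choice is defensible if it is made before the results are seen.

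The cost is a wording change, slightly more follow-up and one extra analysis. One of the two analysis sets will include a few people later found not to have migraine.
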